### Interventions

2.4

The experimental group will receive ART session for 20 minutes, followed by usual physiotherapy for 40 minutes. The ART will be conducted in a quiet room. Participants will be positioned in supine lying or sitting throughout the session and should empty his or her bladder before the session. During the ART session, the participants are asked to loosen any tight clothing, remove watch, spectacles, and stockings. The participants are allowed to close their eyes but not fall asleep while listening to the ART instructions.

Generally, there are 6 standard exercise tasks in ART:

Tranquility exercise: should create a state of silence and concentration. Typical imagination: “I am calm. Nothing can disturb me.”Heaviness exercise: should create a sense of heaviness in the limbs. Typical imagination: “My arms and legs are heavy.”Warmth exercise: sense of heat in the limbs. Typical imagination: “My arms and legs are warm.”Breathing exercise: concentrated breathing. Typical imagination: “My breath is calm and regular.”Heart exercise: Should cause further sedation. Typical imagination: “My heart beats calmly and regularly.”Solar plexus exercise: concentration on the celiac plexus should deepen the relaxation. Typical imagination: “The center is warm.”

After the ART session, the participants will be asked to remain on the training mat for 5 minutes before starting usual physiotherapy interventions. Usual physiotherapy in this study consists of general functional exercises, balance, upper limb, and gait training.

The control group will undergo usual physiotherapy alone for 60 minutes. The content of usual physiotherapy is similar to that given to the ART-added physiotherapy group. Blood pressure of each participant will be recorded before and after the intervention session. The participants are instructed to report any unusual feelings that they may experience such as giddiness, nausea, or shortness of breath to the physiotherapist during the intervention sessions.

Both groups undergo the given intervention for 3 times per week (1 supervised and 2 non-supervised) for 12 weeks, for a total duration of 1 hour per session. Monitoring of the participants will be done weekly during the supervised session to ensure adherence to the non-supervised in-home sessions and to assess the occurrence of any adverse effect.

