**Methods::**

This is an assessor blinded randomized controlled trial comparing 2 intervention approaches namely ART-added physiotherapy (experimental group) and usual physiotherapy (control group). A total of 70 post-stroke patients will be recruited and allocated into either the ART-added physiotherapy or the usual physiotherapy group. The ART-added physiotherapy group will undergo a 20-minute ART session followed by 40 minutes of usual physiotherapy. While the usual physiotherapy group will receive usual physiotherapy alone for 60 minutes. All participants will be treated once a week and are required to carry out a set of home exercises for 2 times per week during the 12-week intervention. Assessment of emotional status and functional independence will be carried out at pre-intervention and week 13 of the intervention with the use of Hospital anxiety and depression scale, Barthel index, and EuroQol-5 dimensions-5 levels. All data will be analyzed using descriptive and inferential statistics.

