### Study design and setting

2.1

A single blind randomized controlled trial will be used as the study design to identify the effectiveness of the ART in addition to usual physiotherapy on post-stroke individuals and comparing this with usual physiotherapy alone. This study will be conducted at Universiti Kebangsaan Malaysia Medical Center, a teaching hospital in the Klang Valley, Malaysia. A one group experimental pilot study will be conducted to identify the feasibility of the ART-added physiotherapy protocol before the main study commences. The flow of the study is shown in Fig. 1.

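### The stated question is whether ART helps when added to usual physiotherapy, but the arms compare ART in place of a third of each supervised physiotherapy session

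*Protocol article*

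**What the plan says.** **The question.** Section 2.1 (Study design and setting) gives the purpose as "to identify the effectiveness of the ART in addition to usual physiotherapy on post-stroke individuals", with physiotherapy alone as comparator. The abstract's introduction and the opening of the Discussion pose the same add-on question, and the Discussion's closing paragraph words its prediction that way. The experimental arm is called ART-added physiotherapy throughout.

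**The arms.** Section 2.4 (Interventions) states: "The experimental group will receive ART session for 20 minutes, followed by usual physiotherapy for 40 minutes". For the other arm: "The control group will undergo usual physiotherapy alone for 60 minutes". On what the physiotherapy contains: "The content of usual physiotherapy is similar to that given to the ART-added physiotherapy group". The abstract gives the same division: "The ART-added physiotherapy group will undergo a 20-minute ART session followed by 40 minutes of usual physiotherapy".

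**The timing.** Section 2.4 schedules three sessions a week in both groups, one supervised and two not, "for 12 weeks, for a total duration of 1 hour per session". It also places a pause in the experimental session: after ART, "the participants will be asked to remain on the training mat for 5 minutes before starting usual physiotherapy interventions".

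**The concern.** An add-on comparison holds the background treatment constant and varies only the added component. Here the physiotherapy is similar in content but shorter in the experimental arm. The between-group difference therefore combines any effect of ART with any effect of having less physiotherapy.

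This matters most for function. The Introduction treats therapeutic exercise as the main means of reducing disability after stroke. The displaced time is functional, balance, upper limb and gait training, and functional independence is an outcome, measured by the MBI. The two effects could therefore pull the MBI in opposite directions.

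A conclusion in add-on terms would not follow from such a contrast. Even a favourable result would carry a different practical message, namely that part of a session can be exchanged for ART.

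**Working it through.** **Inputs, all from section 2.4**
- Experimental arm: ART 20 min, pause 5 min, physiotherapy 40 min.
- Control arm: physiotherapy 60 min.
- Sessions: 3 per week × 12 weeks = 36, of which 12 are supervised and 24 are at home.
- Stated session length: 60 min in both groups.

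**Step 1. The stated hour.**
- Control: 60 min, which agrees.
- Experimental, leaving out the pause: 20 + 40 = 60 min, which agrees.
- Experimental, with the pause where the text puts it: 20 + 5 + 40 = 65 min, which does not agree.

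Three readings are open:
- the pause is inside the ART block (15 + 5 + 40 = 60);
- it is inside the physiotherapy block (20 + 5 + 35 = 60);
- it lies outside the hour (65 in all).

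The text does not say which.

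**Step 2. Physiotherapy per supervised session.** 60 − 40 = 20 min less, and 20/60 = 33%. If the pause came out of physiotherapy, the figure would be 60 − 35 = 25 min, and 25/60 = 42%.

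**Step 3. Physiotherapy over 12 weeks.** The abstract describes the unsupervised sessions only as home exercises, and the article does not say how they are divided in the experimental arm. Taking 40 min of physiotherapy per split session, the two ends are:

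| Assumption about home sessions | Experimental | Control | Shortfall |
|---|---|---|---|
| 60 min of exercise in both arms | (12 × 40 + 24 × 60)/60 = 32 h | 36 × 60/60 = 36 h | 4 h (4/36 = 11%) |
| Same 20/40 split in all 36 sessions | 36 × 40/60 = 24 h | 36 h | 12 h (12/36 = 33%) |

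**Step 4. What the difference estimates.** Let A be the effect of adding 20 min of ART with physiotherapy held constant, and P the effect of the physiotherapy minutes that the experimental arm does not receive. If the two effects simply add (an assumption made for illustration):
- an add-on trial estimates A;
- this trial estimates A − P.

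The two agree only if P = 0. If P is positive, a null result means A = P, not A = 0, and a negative result is compatible with a positive A. A favourable result would still imply A > 0. The article gives no figure for P on the MBI or any other outcome, so the gap between the two questions cannot be put in MBI points.

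**The case against.** Matching session length is a legitimate choice. A pure add-on design would give the experimental arm more contact time, and that alone might move self-reported scales such as the HADS and EQ-5D-5L. The split is stated openly in the abstract and again in section 2.4. The sentence in the Introduction that formally states the aim speaks of ART combined with physiotherapy, which fits the arms better. The consequence is also narrow: it falls mainly on a null or negative MBI result, and no figure in the article shows that 20 fewer minutes per session changes the MBI.

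Most of this stands, and it limits the point to how the question and conclusion are worded. It does not remove the point. Disclosing the split does not correct the add-on question posed in the abstract, section 2.1 and the Discussion, and one looser sentence in the Introduction does not override them.

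A reader might infer three stronger things that the document does not support:
- **That the comparison is invalid.** It is a valid randomised comparison of two sessions stated to be of equal length; only the add-on interpretation fails.
- **That the 65-minute sum shows unequal contact time, or that physiotherapy is really 35 minutes.** The pause could equally be counted within the ART block. The 5 minutes also have no bearing on which question is tested.
- **That the experimental arm loses 12 hours of physiotherapy.** That is the upper end of a range and depends on an undescribed split of the home sessions.

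**Conclusion.** The concern holds as a mismatch between the stated question and the contrast. The trial as described estimates the net effect of replacing a third of each supervised physiotherapy session with ART at matched session length. It does not estimate the effect of adding ART to unchanged physiotherapy.

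The 33% per supervised session follows directly from the stated minutes. The 12-week range of 4 to 12 hours rests on the two assumptions about home sessions and on 40 minutes of physiotherapy per split session. Whether the lost time affects function is plausible on the article's own reasoning but is not quantified there. The 65 v 60 minute discrepancy is real, minor and separate.

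**What to change.** Reconcile the stated question with the arms. With the arms as described:
- word the aim, the hypothesis and the eventual conclusion as ART replacing part of a physiotherapy session of equal length, wherever the add-on phrasing or arm name now suggests otherwise;
- interpret the MBI result as a net effect, and do not read a null or negative result as evidence that added ART has no benefit.

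Separately, reconcile the 20, 5 and 40 minutes with the one-hour session by stating where the pause falls. No view is offered here on which duration is right.

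The cost is rewording only. No extra participants, assessments or changes to the analysis are needed.

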### Outcomes

2.5

Feasibility of the intervention will be assessed with regards to the participants’ acceptance and adherence, the occurrence of adverse effect and feedback from the participants.

Outcomes of the main study will be measured as follows:

The anxiety level will be measured using Hospital anxiety and depression scale (HADS), a self-reported questionnaire and most reliable instrument to identify the presence of depression and anxiety in outpatient department.^[25]^ The scoring can be classified as normal (0–7), borderline (8–10), and caseness (≥11).^[26]^ The recommended cut off score for Hospital anxiety and depression scale is ≥8. The tool has established validity and reliability, with a reliability score of 0.88 for anxiety subscale and 0.79 for depression subscale.Modified Barthel index (MBI) will be used to measure functional independence of the participants. MBI is a tool to measure the degree of assistance needed by a person, with using 10 specific activities of daily living. Each component is scored by numerical scale and the total score ranges from 0 to 20. The classification is based on physical disability; no physical disability (20), mild impairments (15–19), moderately disabled (10–14), severe disability (5–9), and very severely disabled (0–4). MBI demonstrates high test-retest reliability and inter-rater reliability.^[27,28]^EuroQol 5-Dimension 5 Levels (EQ5D5L), a standardized instrument for measuring generic health status will be used to measure quality of life of the participants. The descriptive system comprises 5 dimensions of life namely mobility, self-care, usual activities, pain/discomfort, and anxiety/depression. Each dimension has 5 levels of response: no problems, slight problems, moderate problems, severe problems, and extreme problems. The respondent is asked to indicate his/her health state by ticking (or placing a cross) in the box against the most appropriate statement in each of the 5 dimensions. This response results in a 1-diginumber expressing the level selected for that dimension. The digits for 5 dimensions can be combined in a 5-digit number describing the respondent's health state, termed health utility index. All dimensions of the EQ5D5L are reliable in test–retest with intraclass correlations ranging from 0.67 to 0.81.^[29]^

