### Sample size

2.7

The one group experimental pilot study involves 20 participants which is considered adequate to assess the feasibility of a pilot intervention.^[30]^ For the main study, 70 eligible stroke participants will be recruited. The sample size of 70 was estimated using GPower software and based on mixed-model analysis of variance (ANOVA) test with effect size of 0.34 (Manzoni 2008),^[31]^ significance level *P* < .05 and study power 80%.

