### Data analysis

2.8

All data will be entered into IBM Statistical Packages for Social Sciences (SPSS) version 25.0. Intention-to-treat (ITT) method will be used; all the participants recruited at baseline will be included in the outcome analysis. Using ITT, missing data will be replaced with last observation carried forward. Socio-demography and health profile of the participants will be analyzed descriptively and reported as frequencies (percentages) and mean (standard deviation) or median (inter-quartile range). The effects of the interventions will be analyzed using mixed model ANOVA and reported as main time, group, and time–group interaction effects. The level of significance will be set as *P* < .05 for all results.

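### The article defines the EQ-5D-5L five-digit health-state code as a utility index; it is a categorical label and not a score that an ANOVA can use

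*Protocol article*

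**What the plan says.** Section 2.5 (Outcomes) introduces the EQ-5D-5L as "a standardized instrument for measuring generic health status will be used to measure quality of life of the participants". It lists "5 dimensions of life namely mobility, self-care, usual activities, pain/discomfort, and anxiety/depression", adds that "Each dimension has 5 levels of response", and explains that each answer becomes one digit. It then defines the summary: "The digits for 5 dimensions can be combined in a 5-digit number describing the respondent's health state, termed health utility index". The article mentions no value set, level sum or visual analogue scale.

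Section 2.8 (Data analysis) gives one named method for treatment effects: "The effects of the interventions will be analyzed using mixed model ANOVA and reported as main time, group, and time–group interaction effects". It also says "The level of significance will be set as *P* < .05 for all results". It does not say which EQ-5D-5L variable enters the model.

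The Abstract lists the EQ-5D-5L among the instruments used before the intervention and at week 13. The Discussion anticipates an improvement in quality of life.

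**The concern.** A utility index is a number on a value scale, usually obtained by passing the health state through a published value set. The five-digit code is the input to that step and not its result. The article gives the name of the result to the input.

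This matters because an ANOVA needs a numeric variable with meaningful distances, and the code is the only candidate the article offers. An analyst who took section 2.5 at its word would average codes such as 21231. One level of mobility would then count 10,000 units and one level of anxiety/depression 1 unit. The dimension closest to the emotional target of the relaxation training would drop out of the quality-of-life result.

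**Working it through.** **Inputs.** Five dimensions with five levels each, in the order listed (section 2.5), so 5^5 = 3125 possible states. Total N = 70 (section 2.7), taken as 35 per arm; equal allocation is an assumption.

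**The plan's own figure.** The article states no EQ-5D-5L figure. Its one calculated number, N = 70 for an "effect size of 0.34" and 80% power, can be reproduced in two ways:

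- f = 0.34 in a two-group F test: noncentrality 0.34² × 70 = 8.092.
- d = 0.34, so f = 0.17, in a group-by-time interaction with two measurements and an assumed correlation of 0.5: 0.17² × 70 × 2 / (1 − 0.5) = 8.092.

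Both have 1 and 68 degrees of freedom and power 0.801. Neither depends on how the EQ-5D-5L is scored.

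**What the code measures.** With digits in the listed order,

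code = 10,000·mobility + 1,000·self-care + 100·usual activities + 10·pain/discomfort + 1·anxiety/depression.

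If the five dimensions vary equally and independently, their variance contributions are in the ratio 10^8 : 10^6 : 10^4 : 10^2 : 1, with sum 101,010,101.

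| Dimension | Share of the code's variance |
|---|---|
| Mobility | 0.990 |
| Self-care | 0.0099 |
| Usual activities | 9.9 × 10⁻⁵ |
| Pain/discomfort | 9.9 × 10⁻⁷ |
| Anxiety/depression | 9.9 × 10⁻⁹ |

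**Sensitivity to the equal-variance assumption.** Section 2.2 excludes a modified Rankin score of 4 or more, which may narrow the mobility range. If mobility has r times the variance of each other dimension, its share is r·10^8 / (r·10^8 + 1,010,101):

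- r = 0.25: 25,000,000 / 26,010,101 = 0.96
- r = 0.10: 10,000,000 / 11,010,101 = 0.91

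Mobility dominates throughout this range.

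**Ordering of states.** Higher levels are worse.

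- 15555 (extreme problems on four dimensions) has level sum 21, and 21111 (a slight mobility problem only) has level sum 6. As numbers, 15555 < 21111, so the code ranks the first state as better.
- 11115 (extreme anxiety/depression only, level sum 9) is likewise below 21111.

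With all 3125 states equally likely, the code correlates with the level sum at 11,111 / (√5 × √101,010,101) = 0.49. In 500,000 randomly drawn pairs, the code and the level sum disagreed on order in 29% of the pairs with different level sums.

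**Effect on power.** For illustration, take an effect of 0.68 SD on one dimension only (d = 2f with f = 0.34). Under independence and equal variances, the standardised effect on the code is 0.68 × weight / √101,010,101. Power in the direction of the effect is Φ(d·√(35/2) − 1.96).

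| Effect confined to | Score analysed | d | Power |
|---|---|---|---|
| Mobility | code | 0.677 | 81% |
| Self-care | code | 0.068 | 4.7% |
| Anxiety/depression | code | 0.00007 | 2.5% |
| Any one dimension | level sum | 0.68/√5 = 0.304 | 25% |

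The 2.5% for anxiety/depression is the false-positive rate in one direction: the code cannot detect such an effect. The level sum also dilutes an effect on a single dimension, but it treats all five alike.

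**The case against.** The strongest reply is that nothing in the article commits the trial to analysing the code. A reader might put sections 2.5 and 2.8 together and infer that the raw code will enter the ANOVA, so that the quality-of-life result will be meaningless. The documents do not support that as a statement of fact. Section 2.5 says only that the digits can be combined, which describes the instrument. Section 2.8 names no EQ-5D-5L variable. The word utility suggests that the authors had a real index in mind and lost the conversion step when condensing the protocol. This part of the objection stands, and the consequences calculated above are therefore conditional.

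It is also fair that an article may leave the choice of value set to the full protocol or the analysis plan, neither of which is shown. The absence of a named value set is not the finding.

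Two further points reduce the weight. The code never misorders two states when one is at least as bad on every dimension and worse on at least one; the misordering arises only when dimensions trade off. And the five answers are recorded in any case, so a proper index can be derived later without loss.

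None of this removes the defect. The article is not silent: it defines the index, and defines it wrongly. An analysis plan that followed the definition would analyse a label, and one that used a value set would contradict it.

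**Conclusion.** The definition in section 2.5 is wrong as written and should be corrected; severity is moderate. That the code is a label and not a utility rests on no assumption. The size of the harm applies only if the code is analysed as a number. In that case mobility would supply about 99% of the variance under equal, independent variances, and still about 91% if its variance were a tenth of the others'. Anxiety/depression would have practically no weight, and some states would be ranked perversely. These figures also assume that the digits are joined in the listed order. The article gives no EQ-5D-5L data against which to test the variance assumptions.

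The point is confined to quality of life. The HADS and modified Barthel analyses and N = 70 are unaffected.

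**What to change.** Replace the sentence in section 2.5 with wording such as: The five-digit profile describes the health state and is reported descriptively only. The score entered in the planned analysis is the utility index obtained from the profile with a named published value set, fixed before unblinding. If no suitable value set is used, the level sum score (5 to 25) is analysed instead.

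One of the two scores should be chosen and named, so that the choice cannot depend on the results. Section 2.8 can then name that score as the EQ-5D-5L variable in the mixed-model ANOVA. This point requires no change of model.

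The cost is a few words and a scoring look-up. No further data, visits or participants are needed.

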### Assessment of outcomes

2.6

Participants will be assessed at baseline and at week 13 of interventions by a therapist who is blinded to the group allocation and trained to conduct the standardized tests. The recorded baseline assessment data will not be accessible to the blinded assessor at post-trial assessment in view to avoid assessment bias.

### Sample size

2.7

The one group experimental pilot study involves 20 participants which is considered adequate to assess the feasibility of a pilot intervention.^[30]^ For the main study, 70 eligible stroke participants will be recruited. The sample size of 70 was estimated using GPower software and based on mixed-model analysis of variance (ANOVA) test with effect size of 0.34 (Manzoni 2008),^[31]^ significance level *P* < .05 and study power 80%.

